#### Recruitment

Postural assessments will be performed at the various locations of the participating musicians’ orchestras.

### Data Collection, Management, and Analysis

All collected data (demographic, clinical, postural, and questionnaire data) will be managed to ensure participant confidentiality. Data collection will use Research Electronic Data Capture (REDCap; Vanderbilt University), hosted on a secure server at Fondazione Don Carlo Gnocchi. Each participant will be assigned a unique study ID. The key linking the ID to personal identity will be stored in a password-protected file, separate from the research database, accessible only to the principal investigator. All data will be pseudonymized for analysis.

Photographs taken for postural assessment are considered sensitive personal data. Raw images containing faces will be accessible only to designated medical personnel and the enrolling therapist directly involved in the study. In accordance with the approved ethical protocol, all raw photographs will be permanently deleted upon completion of data analysis. The pseudonymized postural measurement dataset and questionnaire responses will be retained for 10 years after study conclusion for archival purposes, as required by Italian regulation and the funding body, on the secure institutional servers.

### Statistical Methods

Statistical analysis will be performed using SPSS Statistics software (version 27.0; IBM Corp). The primary analysis will focus on within-subject comparisons of postural parameters measured in the 2 experimental conditions (without instrument vs with instrument). Continuous variables will be described using the mean and SD or the median and IQR based on their distribution. The Kolmogorov-Smirnov test will be used to assess the normality of the distributions. Categorical variables will be reported in terms of relative frequencies.

### Main Comparison: Postural Changes With and Without the Instrument

To address the primary objective of quantifying postural deviations induced by instrument playing, postural measurements obtained in the 2 conditions will be compared using paired statistical tests. Specifically, for continuous postural parameters such as shoulder height difference, cervical arrow, and scapula-rachis distance that are normally distributed, the 2-tailed paired *t* test will be used. For parameters deviating from normality, the Wilcoxon signed-rank test will be applied. These analyses will be conducted on the entire sample and subsequently stratified by instrument category (symmetric vs asymmetric) to elucidate instrument-specific effects. For each parameter, the magnitude of postural change will be calculated as the delta value, defined as the measurement obtained with the instrument minus that obtained without the instrument. These delta values constitute the primary measures of playing posture and will serve as key independent variables in subsequent regression models.

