**Conclusions:**

This study will provide quantitative insights into postural deviations and their relationships with pain and pain leading to performance limitation. The findings are expected to identify instrument-specific associated factors and compensatory behaviors, supporting the development of targeted ergonomic interventions and preventive strategies for musicians’ health.

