#### Sample Size

A total of 250 participants will be enrolled. Regarding the primary objective of the study, which is to investigate the prevalence and types of postural alterations, it is estimated that—assuming a prevalence of 50%—a sample of 250 participants will allow for an estimation of the prevalence with a significance level of α=5% and a precision (semiwidth of the CI) of 6%, using the binomial model with normal approximation for the calculation of the CI.

Participant recruitment will be conducted following ethics committee approval and registration of the study on ClinicalTrials.gov, with an anticipated recruitment period of 30 months.

Participation in the study will be voluntary and will require written informed consent. All musical instruments will be eligible for inclusion and will be classified as either symmetrical or asymmetrical for analysis purposes.

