### Association With Pain and Disability (Secondary Aims)

To examine factors associated with the outcomes of pain and performance-limiting pain, logistic regression models will be used. The dependent variables will be the presence of pain during the preceding week and the presence of performance-limiting pain during the preceding week, both operationalized as binary outcomes. Independent variables will include demographic characteristics (eg, age and gender), occupational factors (eg, instrument type [classified as symmetric or asymmetric], years of professional experience, and practice hours), and postural delta values, which represent instrument-induced postural changes as described above.

To investigate factors associated with the severity of disability, as measured by the QuickDASH, Oswestry Disability Index, and Neck Disability Index scores, linear regression models (or quantile regression models, if model assumptions are violated) will be used, incorporating the same set of independent variables.

Variables achieving a *P* value of <.10 in univariate analyses will be entered into multivariable models to identify independent predictors. Results will be reported as odds ratios or regression coefficients with their corresponding 95% CIs. A *P* value of <.05 will be considered indicative of statistical significance in all final models.

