## Discussion

### Anticipated Findings

This study is designed to provide a comprehensive quantitative analysis of postural deviations in professional orchestral musicians and to explore their association with pain and PPL. By systematically comparing posture during instrumental performance and in a neutral, instrument-free condition, the study aims to identify posture-related associated factors, compensatory strategies, and their potential impact on musicians’ health and professional functioning.

Beyond estimating the prevalence of postural alterations, pain, and PPL, this investigation seeks to clarify how instrument-specific demands and asymmetrical playing positions influence musculoskeletal load. The comparison between neutral sitting posture and instrument-related posture is expected to highlight the extent to which musical performance exacerbates or induces postural deviations, thereby contributing to biomechanical strain. This distinction may help differentiate between baseline postural characteristics and those primarily driven by instrumental practice.

The anticipated findings may reinforce existing evidence that prolonged exposure to forced and asymmetrical postures represents a major contributor to musculoskeletal disorders in musicians. Instruments requiring sustained elevation of the upper limbs, trunk rotation, or unilateral loading—such as bowed string and certain wind instruments—are likely to be associated with greater degrees of postural imbalance, particularly at the cervical, shoulder, and scapular levels. These deviations may correlate with higher rates of upper limb and spinal pain, supporting the hypothesis that compensatory postural behaviors act as a key intermediate mechanism linking instrumental demands to PRMDs.

A central aspect of this study is the investigation of compensatory strategies adopted by musicians to meet technical and artistic performance requirements. While these adaptations may allow musicians to maintain performance quality in the short term, they may also increase cumulative musculoskeletal load over time, predisposing individuals to PRMDs. The identification of such compensatory patterns through objective postural measurements may therefore provide clinically meaningful insights that complement self-reported symptoms and disability assessments.

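### Instrument-specific effects are to be read from separate paired tests in symmetric and asymmetric players; the postural change itself is never compared between the two categories

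*Protocol article*

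**What the plan says.** The section on the main comparison (postural changes with and without the instrument) sets the method for continuous parameters: "the 2-tailed paired *t* test will be used. For parameters deviating from normality, the Wilcoxon signed-rank test will be applied". The same section then gives the route to instrument effects: "These analyses will be conducted on the entire sample and subsequently stratified by instrument category (symmetric vs asymmetric) to elucidate instrument-specific effects".

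That section also defines a delta for each parameter, with-instrument minus without-instrument, and gives its further use: "These delta values constitute the primary measures of playing posture and will serve as key independent variables in subsequent regression models". Those regressions, described under the secondary aims, have pain, performance-limiting pain and disability scores as outcomes. Instrument type enters them as a predictor of those outcomes, not of postural change.

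The section on multiple postural measures calls all of them exploratory. It offers an optional repeated-measures multivariate analysis of variance between conditions, promises Bonferroni or Benjamini-Hochberg correction for multiple paired comparisons, and adds paired Cohen d beside P values.

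Instrument-level conclusions are anticipated. The Discussion states that "this investigation seeks to clarify how instrument-specific demands and asymmetrical playing positions influence musculoskeletal load", and the abstract's conclusions say: "The findings are expected to identify instrument-specific associated factors and compensatory behaviors".

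**The concern.** An instrument-specific effect means that the postural change differs by instrument category. A paired test in symmetric players and another in asymmetric players each compare one change with zero. Neither compares the two changes with each other.

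Two errors can follow:

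- **False contrast.** The two categories shift equally, but one test crosses the significance threshold and the other does not, through chance or because one group is smaller.
- **Missed contrast.** Both categories shift, one by much more, and both tests are significant, so the results look alike.

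The article names the within-category tests as the means to this end. This is therefore a stated method that does not fit its stated purpose, not a detail left to a fuller document. At stake is any statement in the results that one category alters posture more than the other.

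**Working it through.** **1. Is a between-category comparison of delta planned anywhere in the article?**

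- Main comparison: paired tests overall, then within category. No between-category test.
- Interventions and outcomes: postural measures are to be analysed by the symmetric/asymmetric classification. No test is named.
- Multiple postural measures: the optional multivariate analysis compares conditions. No condition-by-category term is named.
- Secondary aims: category predicts pain and disability, not delta.
- Abstract: t tests and chi-square tests are listed without being tied to this contrast.

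None supplies it.

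**2. The plan's own sample-size figure.** The Sample Size section sets the total ("A total of 250 participants will be enrolled") and justifies it by precision alone, with a stated half-width of 6% for an assumed prevalence of 50%. Half-width = 1.96 × √(0.5 × 0.5 / 250) = 0.062, which rounds to the stated 6%. The 250 was not sized for a comparison between categories.

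**3. Chance of a false contrast.**

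Inputs:

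- Total of 250, from the Sample Size section.
- Split between categories: not given. Assumed 125/125 and 187/63.
- Standardized change d (mean delta / SD of delta), the same in both categories: not given. Assumed 0.2 to 0.5.
- Two-sided .05, uncorrected. The article fixes this level for the regressions ("A *P* value of <.05 will be considered indicative of statistical significance in all final models"); for the paired tests it is an assumption.

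Power in a category of size n comes from the non-central t distribution with n − 1 degrees of freedom and non-centrality d√n. With powers p1 and p2, P(exactly one significant) = p1(1 − p2) + p2(1 − p1).

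Worked case, d=0.25:

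- 125/125: p1 = p2 = .792, so 2 × .792 × .208 = .329.
- 187/63: p1 = .925, p2 = .497, so .925 × .503 + .497 × .075 = .502 (from unrounded powers).

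| True d in both categories | 125/125 | 187/63 |
|---|---|---|
| 0.2 | 48% | 59% |
| 0.25 | 33% | 50% |
| 0.3 | 16% | 36% |
| 0.4 | 1% | 12% |
| 0.5 | about 0% | 3% |

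A direct two-sample test of the deltas has a nominal false-positive rate of 5% in these settings. Simulation with 20,000 replicates, over splits of 125/125, 75/175 and 50/200 with d of 0.2 or 0.25, gave 4.8% to 4.9%.

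**4. Does the planned correction remove it?** Take 14 parameters, an assumed count: eight frontal and four sagittal measures, plus trunk rotation and shoulder asymmetry. Bonferroni gives .05/14 = .0036. At d=0.3:

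- 125/125: power .649 in each, so 2 × .649 × .351 = 46%.
- 187/63: powers .873 and .270, so .873 × .730 + .270 × .127 = 67%.

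Correction moves the problem to somewhat larger effects and does not remove it.

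**5. Chance of a missed contrast.** With true d of 0.4 and 0.8 and 125/125 players, the within-category powers are .993 and about 1.000. Both tests are significant in about 99% of studies, so no contrast appears. The direct test of the 0.4 SD difference has 88% power.

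**The case against.** The strongest reply has four parts.

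- **The article sets no rule for reading discordant strata.** It does not say that a contrast will be declared when one category is significant and the other is not, and a full analysis plan, not shown, might compare the deltas. The first part stands: that reading is a risk, not a stated intention. The second does not dispose of the point, because the article itself names the stratified paired tests as the route.
- **The plan discourages reliance on significance.** Measures are exploratory, findings are to be read with caution, and paired Cohen d is reported. This stands as mitigation. Two stratum effect sizes set side by side still give no estimate of their difference and no interval for it.
- **The contrast is not a stated aim.** This stands. A reader might infer from the Discussion and the abstract that a symmetric-versus-asymmetric difference is a headline conclusion. The objectives list postural change with and without the instrument and its association with pain, and the within-subject comparison is primary. The two anticipatory sentences speak of musculoskeletal load and associated factors, not of a difference in delta between the two categories.
- **The risk is confined to small changes.** This stands in part. At uncorrected .05 it has nearly gone by d=0.5 for the splits tabulated, and some parameters may shift by more than that between relaxed arms and a playing position. The article gives no figure, and the risk of missing a real contrast grows as changes become larger.

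A reader might also argue that choosing between the t test and the Wilcoxon test on the normality of the parameters is what lets the two strata be tested differently. That does not follow: checking normality of the paired differences within each stratum could also select different tests.

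**Conclusion.** The point holds in a limited form. The article assigns instrument-specific effects to tests that cannot estimate them, and nothing else in it compares delta between categories.

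With equal true changes, the chance of discordant results runs from 48% (125/125) or 59% (187/63) at d=0.2 down to about 0% or 3% at d=0.5. These figures rest on an assumed split, an assumed common d and two-sided .05 without correction. A false contrast can arise; it does not follow that every discordant result is false, since discordance may also reflect a real difference.

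The analysis is subsidiary and exploratory. The overall with-versus-without comparison and the prevalence estimate are not affected.

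**What to change.** For each postural parameter, regress delta on instrument category, which is equivalent to testing the condition-by-category interaction. Report the between-category difference in delta with its 95% CI as the instrument-specific result, and bring these comparisons under the Bonferroni or Benjamini-Hochberg procedure already planned. Keep the within-category means, tests and Cohen d as description.

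The cost is one extra model per parameter, on a delta the plan already computes, and no new data. Precision will be limited because the 250 was set for a prevalence interval. The difference detectable with 80% power at two-sided .05, uncorrected, is about (1.96 + 0.84) × √(1/n1 + 1/n2) SDs of delta: 0.35 for 125/125 and 0.41 for 187/63, and larger after correction. The interval should therefore be reported even when the test is not significant. The Results section says that analysis is under way, so the change should be dated and recorded as made at that stage.

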Research confirms that prolonged forced body positions increase the likelihood of musculoskeletal overload. Few studies focus on the impact of playing classical instruments on posture [9]. Musicians spend about 1300 hours per year in ergonomically unfavorable positions. Instruments requiring different playing positions and techniques have varying prevalence rates of musculoskeletal disorders [10]. A study among conservatory students found high rates of postural alterations without the instrument (66.2%) and nonoptimal posture with the instrument (73.4%). Asymmetrical postures, such as those required by the violin, viola, and flute, are significant associated factors [11].

Musicians playing with arms above the scapulohumeral plane are more prone to PRMDs in the upper limbs [12]. Addressing these conditions requires understanding the factors and implementing appropriate measures. Reviews on ergonomic assessment in orchestra musicians indicate a lack of publications on this topic [13]. More information is available on questionnaires assessing symptoms, such as the “standardized Nordic Musculoskeletal Questionnaire” [14] and the Disabilities of the Arm, Shoulder, and Hand [15].

Compensatory behaviors can be a significant associated factor linked to musculoskeletal disorders among musicians. Understanding and addressing these behaviors is essential for effective prevention and management.

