Participants were seated on a standardized stool (height: 47 cm; leg separation: 26.5 cm), except for the double bass players who used a chair provided by the orchestra without a backrest due to the instrument’s size and ergonomic requirements. The stool, the chair, and the camera were placed in fixed positions, which were marked on a mat included in the kit, and the instrument was calibrated according to these distances.

For photos without the instrument, participants kept their arms relaxed alongside the body. For photos with the instrument, hand placement followed the standard playing position (a position for string instruments). In both phases, the Physical Analyzer Portable will be used—a noninvasive, portable device that allows calibrated photo acquisition on the frontal and sagittal planes and subsequent data processing through dedicated software. This device is not formally validated but it is aligned with the principles of clinical posture assessment presented in the study by Fortin et al [19]. The following measurements will be taken with and without the musical instrument.

As far as the frontal plane is concerned, the following parameters will be measured: trunk inclination on the frontal plane: angle between C7 and IG, head-neck inclination: angle between ST and GL, right shoulder height: distance between RS and the horizontal line passing through C7, left shoulder height: distance between LS and the horizontal line passing through C7, right shoulder width: distance between RS and the vertical line passing through C7, left shoulder width: distance between LS and the vertical line passing through C7, right scapula–rachis distance: distance between RIA and the vertical line passing through C7, and left scapula–rachis distance: distance between LIA and the vertical line passing through C7.

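### The postural delta is a signed difference pooled without regard to loaded side, so lateral changes may be understated and a link between pain and deviation in either direction may be missed

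*Protocol article*

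**What the plan says.** The section on the main comparison states that "the magnitude of postural change will be calculated as the delta value", and then defines that value as "defined as the measurement obtained with the instrument minus that obtained without the instrument". The tests are set out in the same section: "postural measurements obtained in the 2 conditions will be compared using paired statistical tests", by paired t test or Wilcoxon signed-rank test. On grouping it says "These analyses will be conducted on the entire sample and subsequently stratified by instrument category (symmetric vs asymmetric"). On later use it says "These delta values constitute the primary measures of playing posture and will serve as key independent variables in subsequent regression models".

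The section on association with pain and disability puts the deltas into logistic models for pain and performance-limiting pain, and into linear or quantile models for the disability scores. Instrument enters as symmetric or asymmetric. Variables reach the multivariable model through a univariate screen at P<.10.

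Several parameters under Interventions and Outcomes are lateral: frontal trunk inclination, frontal head-neck inclination, trunk rotation and right-left shoulder asymmetry. Others are distances taken separately on each side, for example "right shoulder height: distance between RS and the horizontal line passing through C7". Of the three core parameters named under Handling of Multiple Postural Measures, head-neck inclination and shoulder asymmetry are lateral, and lumbar arrow is sagittal.

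The background section says "Asymmetrical postures, such as those required by the violin, viola, and flute, are significant associated factors". The article does not say which side each instrument loads, what the instrument mix is, or which direction counts as positive.

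**The concern.** A signed difference is not a magnitude. For a lateral measure, a shift of a given size to the left and the same shift to the right have opposite signs. Averaged over players whose instruments load different sides, they offset each other. The split into symmetric and asymmetric classes does not prevent this, because the asymmetric class is not divided by side.

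The regression problem is separate and larger. One linear term for a signed lateral delta says that if movement one way raises the odds of pain, movement the other way lowers them by the same factor. The article's reasoning (Background and Rationale; Anticipated Findings) is about imbalance and deviation, not one particular direction. If deviation either way matters, this term can miss the association or make one direction look protective, and the P<.10 screen can then remove the variable. Two of the three core parameters are exposed.

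**Working it through.** **The article's own figure.** Its only quantitative design statement is the half-width for a prevalence: 1.96 × √(0.5 × 0.5 / 250) = 6.2%, which matches the stated 6% after rounding. It does not bear on this point. The article gives no effect size or power for the paired tests or the pain models, so the inputs below are assumptions, apart from N = 250 and the two-sided 5% level.

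**Paired tests, general form.** Let a share q of players shift by +d and a share 1−q by −d, with within-side SD 1.

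- Mean delta = d(2q−1)
- SD = √(1 + 4q(1−q)d²)
- Standardised mean dz = mean / SD

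The mean therefore shrinks by the factor 2q−1: to 0 at q = 0.5, 40% of the true shift at q = 0.7 and 60% at q = 0.8. With d = 1 and q = 0.8, the mean is 0.6, the SD is √1.64 = 1.28, and dz is 0.47 instead of 1.0.

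Normal-approximation power in an assumed asymmetric stratum of 125:

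| q | d = 0.5 | d = 1 |
|---|---|---|
| 0.5 | 5% | 5% |
| 0.6 | 17% | 36% |
| 0.7 | 53% | 91% |
| 0.8 | 88% | >99% |
| 1.0 | about 100% | 100% |

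**Worked model in degrees.** Assume 250 players, of whom 60% shift by 8 degrees to one side and the rest have no systematic shift. Add noise of SD 4 and set logit P(pain) = −0.8 + 0.1|delta|.

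At a 60:40 split:

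- Mean = 0.6 × 8 × (0.6 − 0.4) = 0.96 degrees
- Variance = 16 + 0.6 × 64 − 0.96² = 53.5, so SD = 7.31
- dz = 0.131, and dz × √250 = 2.08
- Power ≈ Φ(2.08 − 1.96) ≈ 55%

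The mean absolute delta is 6.1 degrees at any split. Simulation with 400 replicates gives:

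| Side split | Mean signed delta, 4.8 × (2q−1) | Paired test rejects | Logistic power, signed | Logistic power, absolute |
|---|---|---|---|---|
| 50:50 | 0 | 6% | 8% | 88-90% |
| 60:40 | 0.96 | 59% | 7% | 88-90% |
| 75:25 | 2.4 | 100% | 16% | 88-90% |
| 90:10 | 3.84 | not tabulated | 43% | 88-90% |
| 100:0 | 4.8 | not tabulated | 74% | 88-90% |

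Here absolute means |with minus without|. A delta aligned to the loaded side has 71-74% power at every split. The Monte Carlo standard error is at most √(0.25/400) = 2.5 points, and longer runs agree within a few points.

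**Sensitivity to the assumptions.** A second model has all 250 players asymmetric, a shift of 1 SD, and an odds ratio of 1.6 per SD of absolute deviation.

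- Signed-term power is 6% at q = 0.5, 12% at 0.7, 21% at 0.8, 40% at 0.9 and 69% at 1.0. The absolute term has 81-83%.
- At q = 0.8 the signed term passes the P<.10 screen in 32% of runs. The absolute term passes in 88-91%.

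**The case against.** The strongest reply is that the premise is not in the article. It names violin, viola and flute as asymmetrical but gives no side for any instrument and no mix. That stands: every figure above is conditional on an assumed split.

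A reader might infer that the main comparison will show little or no postural change. The figures do not support that. Significance is lost only near balance; at 75:25 the worked model rejects in 100% of runs, and what remains is an understated mean and Cohen d. Nor is every measure affected. The cervical and lumbar arrows are not lateral. The separate right and left distances keep a defined meaning on each side, so pooling blurs laterality in them but does not reverse a sign.

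The regression result also depends on generating pain from absolute deviation. No passage says that this is the true relation, and under a truly directional effect an absolute term would be the less suitable one. This also stands. Even so, the article's interest in imbalance makes an either-direction effect one that the models should be able to detect.

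If the software returns unsigned inclinations, those deltas do not cancel by side. However, a swing from 5 degrees left to 5 degrees right then gives 0. The quantity |with| minus |without| has the same blind spot and is not a general cure.

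Finally, all postural measures are called exploratory, analyses by instrument family are allowed, and coding detail may sit in a fuller document. The family analyses are optional and leave the regressors as they are. The article does not merely omit the coding: it states the formula, the pooling and the regressor.

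**Conclusion.** The point holds in a limited form. The article labels a signed difference a magnitude, pools it without separating loaded sides, and uses it as the posture term for pain and disability. If instruments load different sides, lateral mean changes and Cohen d shrink by an amount that depends on the mix, and vanish only near 50:50.

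The regression weakness is more robust to imbalance. If deviation either way relates to pain, the signed term is well short of the absolute term even at 90:10 (43% against 88-90%), and the gap is modest only when all players load one side (74%). Because the split, the shift and the form of the pain effect are all assumed, this is a should-fix at moderate confidence. The documents do not support calling the primary comparison invalid.

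**What to change.** - State the sign convention for every lateral parameter.
- For the paired tests, align lateral deltas to the side the instrument loads, and recode right and left shoulder and scapula distances as instrument-side and opposite-side. The absolute change should not be tested against zero, because noise alone makes its mean positive.
- In the pain and disability models, replace the raw signed lateral delta with |with minus without|, or with the side-aligned delta. Symmetric instruments have no loaded side, so the absolute form is the one that covers the whole sample.
- Report |with| minus |without| only as change in deviation from neutral, and note that it misses swings across the midline.
- Keep raw signed deltas within groups that load the same side.

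The cost is recoding stored measurements and a few sentences in the plan. Side follows from the instrument played, and no new data are needed. The downsides are two codings to explain and an absolute term that fits less well if the effect on pain is truly directional. The choice should be fixed and dated promptly, since the Results section says that full analysis is already under way.
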